#### Inclusion criteria

Diagnosis of SCD, MCI, or mild AD;Age ≥ 60 years;Visual and auditory acuity adequate for neuropsychological testing;Informed consent provided by the participant or a family member.

#### Exclusion criteria

Severe aphasia, physical disability, psychiatric disorder, suicide attempt, or other factors that could preclude cognitive examination or completion of the SIACI program;Other neurological or psychiatric conditions that could affect cognition (e.g., Parkinson’s disease, stroke, schizophrenia, severe depression, frontotemporal lobe dementia, Huntington’s disease, brain tumors, metabolic encephalopathy, encephalitis, multiple sclerosis, epilepsy, brain trauma, or normal pressure hydrocephalus);Other systemic diseases likely to impair cognition (e.g., hypothyroidism, Wilson’s disease, folic acid or vitamin B12 deficiency, or viral infection [syphilis or HIV]);Alcohol or drug misuse;Participation in another clinical study at the same time;Acute infectious disease or taking nonsteroidal anti-inflammatory drugs or immunosuppressants in the past month (positive results will exclude participants only from the blood biomarker tests);Metal implant or other MRI contraindications (these will exclude participants only from the MRI examination).

#### Sample size determination

The required sample size was estimated using PASS v11.0 (NCSS, Kaysville, UT, USA) based on a completely random design for comparing the means of two independent samples. To our knowledge, there is no previous study on a comprehensive intervention for CIs among older adults in mainland China, so we estimated the effect size of one of the primary outcomes (general cognitive function) based on our previous study that used creative expression therapy to improve MCI patients’ cognitive function [46] . The study was like the planned trial in some respects, as both are RCTs, one of the primary outcomes is general cognitive function, and one of the primary outcome measurement tools (MoCA) is the same. Our previous study [46] found MoCA scores of 24.68 ± 1.84 and 23.13 ± 1.68 in the intervention and control groups, respectively. A sample size of 35 participants per group was determined to be sufficient to detect an effect with a type 1 error rate of 5% (α = 0.05) and 95% power (β = 0.05). Taking into consideration a 20% attrition rate, a total of 88 participants will be needed, with 44 participants per group.

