#### Diagnostic criteria

MCI will be diagnosed based on the Peterson diagnostic criteria of MCI [39], as follows: (1) self-reported memory problems, preferably confirmed by someone close to the participant; (2) memory impairment in accordance with age and education (Montreal Cognitive Assessment [MoCA] [40] score of 13–14 for individuals with no formal education, 19–20 for those with 1–6 years of education, and 24–25 for those with ≥7 years of education); (3) intact activities of daily living (ADL) [41, 42] (ADL score < 25 for age ≥ 75 and < 23 for age < 75); and (4) absence of dementia (Mini-Mental State Examination [MMSE] [43] score of 24–30).

SCD will be diagnosed based on the two major features described by the working group of the Subjective Cognitive Decline Initiative (SCD-I) [44], as follows: (1) a self-experienced persistent decline in cognitive capacity (compared to a previously normal cognitive status), which is unrelated to an acute event, and (2) normal performance on standardized cognitive tests used to classify MCI, adjusted for age, sex, and education.

AD will be diagnosed based on the National Institute of Neurological and Communicative Disorders and Stroke-Alzheimer Disease and Related Disorders Association (NINCDS-ADRDA) diagnostic criteria for probable AD [45], and the presence of mild AD will be determined based on an MMSE score of 21–26.

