### Data collection and analysis

All data analysis will be performed using SPSS Statistics v22.0 (IBM). To ensure that the outcome assessors and data analysts are blinded to group assignment, they will not interact with the participants except, in the case of outcome assessors, during data collection. Demographic and other baseline characteristics will be summarized using descriptive statistics. If necessary, the results will be adjusted for potential confounders, such as age, gender, and education. Between- and within-subject comparisons of the neuropsychological test scores and other outcomes will be conducted using repeated-measures analysis of variance (ANOVA). Statistical analyses will be based on an intention-to-treat (ITT) approach [65], missing data will be imputed by multiple imputation. *P* < 0.05 for two-tailed tests will be considered significant. In sensitivity analyses, we will perform per-protocol (PP) analyses [66], including only the participants who completed the SIACI program and outcome assessment. The details of the fMRI data analysis are displayed in the Additional file.

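### The 95% power rests on a MoCA difference and SD from an MCI-only trial and is not justified for the mixed SCD, MCI and mild AD sample

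*Protocol article*

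**What the plan says.** Under Sample size determination, the Protocol article bases the number of participants on a comparison of two independent means. The inputs are "MoCA scores of 24.68 ± 1.84 and 23.13 ± 1.68 in the intervention and control groups", taken from the team's own earlier trial of "creative expression therapy to improve MCI patients’ cognitive function". The claim is "A sample size of 35 participants per group was determined to be sufficient to detect an effect". Alpha is set at 0.05 and power at 95%. An allowance of 20% for attrition takes 35 to 44 per group, 88 in total. Data collection and analysis makes the test two-sided: "0.05 for two-tailed tests will be considered significant".

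The section says that the earlier trial resembles this one in part. The likenesses it lists are the randomised design, general cognition as a primary outcome, and the MoCA as instrument. The population is not among them.

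Inclusion criteria admit "Diagnosis of SCD, MCI, or mild AD", with no limit on education. Under Diagnostic criteria, MCI needs a MoCA "score of 13–14 for individuals with no formal education, 19–20 for those with 1–6 years of education"; people with seven or more years of schooling must score 24–25. SCD requires normal test performance, and mild AD is set by an MMSE of 21–26.

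The planned analysis is repeated-measures ANOVA. Adjustment is optional, with age, gender and education given as examples. Baseline MoCA and diagnosis are not named.

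**The concern.** Power for an unadjusted comparison depends on the full spread of MoCA scores among those enrolled. The SD used describes MCI patients in one earlier trial. This trial adds a group that tests as normal and a group with dementia. Even within MCI, its criteria place participants anywhere from 13 to 25 according to schooling. A wider spread than 1.76 is therefore likely.

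The 1.55-point difference is also carried over, without stated support, to SCD and mild AD participants, for whom the document offers no effect estimate.

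The 95% figure is the only justification given for 88 participants. Left unqualified, it invites a reader to treat a null result as good evidence of no effect.

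**Working it through.** **Inputs from the document.** MoCA 24.68 (SD 1.84) and 23.13 (SD 1.68); two-sided alpha 0.05; 35 evaluable per group; 20% attrition.

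**Reproducing the plan.**
- Difference: 24.68 − 23.13 = 1.55.
- Pooled SD: √((1.84² + 1.68²)/2) = 1.762.
- Standardised effect: 1.55/1.762 = 0.880.
- Noncentrality: 0.880 × √(35/2) = 3.68 on 68 degrees of freedom, giving power of 95.2% by the noncentral t distribution. With 34 per group it is 94.7%, so 35 is the smallest sufficient number.
- Attrition: 35/0.8 = 43.75, rounded up to 44 per group, 88 in total.

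The stated figures are right for the stated inputs.

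**Unadjusted power at other SDs.** The document gives no MoCA SD for a mixed sample, so these SDs are assumptions. The difference stays at 1.55, with 35 per group and the same two-sided t-test.

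| Total SD | 1.55/SD | Power |
|---|---|---|
| 1.76 | 0.88 | 95% |
| 2.0 | 0.78 | 89% |
| 2.5 | 0.62 | 72% |
| 3.0 | 0.52 | 57% |
| 3.5 | 0.44 | 45% |
| 4.0 | 0.39 | 36% |

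Power is 93% at an SD of about 1.86 and falls below 80% above about 2.28.

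**What the planned repeated measures could recover.** Suppose 1.762 is the SD within a stratum of diagnosis and education, and r is the pre-post correlation within that stratum. Stable differences between strata cancel in a change score, so its SD is 1.762 × √(2(1 − r)), whatever the spread between strata.

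| r | SD of change | Power for 1.55 |
|---|---|---|
| 0.3 | 2.085 | 87% |
| 0.5 | 1.762 | 95% |
| 0.6 | 1.576 | 98% |

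The document gives no value of r.

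**A smaller average effect.** As an illustration, let one third of participants gain nothing and the rest gain 1.55. The mean difference is 1.55 × 2/3 = 1.03 and the standardised effect is 1.033/1.762 = 0.587. Power is about 68%, either unadjusted at SD 1.76 or on change scores at r = 0.5, where the SD is the same. At r = 0.6 it is 77%.

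**The case against.** The strongest reply is that the planned analysis is repeated-measures ANOVA, not a comparison of raw means. In a group-by-time contrast, stable differences by education and diagnosis drop out. The tables above bear this out, so a wide raw SD does not by itself mean low power. This part of the objection stands. It does not rescue the figure as stated, because the calculation claims no such gain and gives no correlation, and the analysis section does not say which contrast is the test. A main effect of group would keep the between-person spread.

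A reader might infer that an SD of 1.76 is impossible given the MoCA bands. That does not follow. Taking band midpoints of 19.5 and 24.5 with a within-band variance of 0.25, a mix of 13% and 87% has variance 0.13 × 0.87 × 5² + 0.25 = 3.08, so the SD is 1.75. The mean is 23.9, between the two means of the earlier trial. Education mixes that give much lower power can be constructed, but the document does not report the mix.

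It is also tempting to combine a total SD of 3.5 with an overall correlation of 0.7 or 0.8, which gives baseline-adjusted power of 72% or 86%. If the extra spread is stable, that understates the recovery. With within-stratum SD 1.762 and r = 0.5, the between-stratum variance is 3.5² − 1.762² = 9.15. The overall correlation is then (9.15 + 0.5 × 3.10)/12.25 = 0.87, the residual SD is 3.5 × √(1 − 0.873²) = 1.71, and power is 96%.

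Finally, the section itself says that no comparable study was known, names the source as MCI patients, and claims only partial similarity. That is fair disclosure of the source. It does not allow for the difference in population.

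**Conclusion.** The concern holds as a mismatch between the inputs and the trial. The 95% belongs to an MCI population and an unadjusted comparison. The trial enrols SCD, MCI and mild AD and plans a repeated-measures analysis, so the figure is not justified for the trial as described.

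How far true power departs from 95% cannot be settled from the document. Unadjusted, it runs from 89% to 36% over assumed SDs of 2.0 to 4.0. On change scores it is 87% to 98% over assumed within-stratum correlations of 0.3 to 0.6, provided that the within-stratum SD is 1.76 and the full 1.55 points apply. The borrowed effect is the part that no adjustment repairs: the one-third illustration gives about 68%.

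A reader might conclude that the trial is underpowered, or that the stated power will not be reached. The document does not support that: it gives no mixed-population SD, no mix of education or diagnosis, and no pre-post correlation. This should be fixed, with moderate confidence.

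**What to change.** Keep 88 participants. In Sample size determination, state that the 1.55-point difference and SD of 1.76 describe MCI patients only, and withdraw the unqualified 95%.

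In Data collection and analysis, make the MoCA comparison baseline-adjusted as a rule and not only when judged necessary.

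Then restate power for that comparison as a short table over three quantities: the within-stratum (residual) SD, the within-stratum pre-post correlation, and an average effect smaller than 1.55. Do not cross a total SD with an independently chosen correlation of 0.6–0.8, because stable spread between strata raises both together.

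The cost is rewording two sections, with no additional participants. The downside is that the stated power may become less favourable.

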#### Randomisation, allocation concealment, and blinding

Ensuring allocation concealment, participants will be randomized (after obtaining written informed consent, eligibility screening, and baseline assessment) to the SIACI and waitlist control groups at a 1:1 ratio by a study staff member (who will not be involved in participant recruitment or outcome assessment) using Research Randomizer software (http://www.randomizer.org/). The participants will then be told their group assignment by the intervention staff. Due to the nature of non-pharmacological interventions, only the outcome assessors and data analysts (not the participants or intervention staff) will be blinded to group allocation.

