### Intervention group

The SIACI program was developed by the research team in consultation with art therapists, neurology experts, and clinical nursing specialists. To ensure standardized administration of the intervention, it will be delivered under the supervision of qualified art therapists by intervention staff who will have received AT training. The intervention staff will be required to complete an intervention-related competency examination before administering the intervention. In each session, the intervention staff will keep a log of the progress and responses of each participant.

AT, with appropriate modifications, is suitable for all dementia phases [27, 47]. Participants with different degrees of CIs will be assigned to different groups corresponding to their ability. The group size will be based on Liebmann’s [48] suggestion that the appropriate number of participants in group activities is 4–12, but if there are experienced group activity facilitators, this can be increased, as long as all participants can maintain visual contact, communicate verbally, and have the opportunity to share and express themselves.

The program will be conducted using neurocognitive function training patterns [49], which integrate bottom-up and top-down approaches (Fig. 2). The program will be divided into three modules, i.e., art experience, art enlightenment, and art exploration, which correspond to the three stages of cognition regulation (perception, comprehension, and application). The AT-based cognitive intervention sessions will be based on the theoretical frameworks of media dimension variables (MDV) (Fig. 2A) and expressive therapies continuum (ETC) (Fig. 2B) [50–53]. The activities will include but not be limited to the following diverse artistic expressive forms: performance arts (music, drama, and dance), visual arts (painting, collage, knitting, sculpture, and pottery), literary arts (novel-writing, poetry, other forms of text-related activities), and the huge range of applied arts (art design, architectural design, and industrial art). Each session will follow the principles of individualization, changing the difficulty/cognitive level from simple to complex, changing the activity structure from highly structured to semi-structured or freestyle, and timely adjustments to adapt to and gradually improve cognitive function.

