To the best of our knowledge, our trial is the first study to assess the effects of an art-based cognitive intervention in different stages of AD and to try to reveal the underlying blood biological and neural mechanisms from a scientific perspective. The trial will employ rigorous methods to reduce bias, such as randomization, proactive recruitment strategies, stringent eligibility screening, innovative theory-based intervention design, blinding of the outcome assessors and data analysts, and statistical analysis according to the ITT principle.

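### Diagnostic stage is fixed neither in the described allocation nor in the analysis covariates, although it is defined partly by two of the primary outcome scales

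*Protocol article*

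**What the plan says.** - **Allocation.** The section on randomisation, allocation concealment and blinding places randomisation after consent, screening and baseline assessment, and assigns participants "to the SIACI and waitlist control groups at a 1:1 ratio by a study staff member" with a named web tool. It mentions no stratum, block or minimisation.
- **Sample size.** The calculation is "based on a completely random design for comparing the means of two independent samples". Its inputs are "MoCA scores of 24.68 ± 1.84 and 23.13 ± 1.68 in the intervention and control groups", taken from an earlier trial of "creative expression therapy to improve MCI" patients' cognition. The result is 35 per group, raised to 44 per group (88 in total) for 20% attrition.
- **Stages.** Under the diagnostic criteria, SCD means normal results on the tests that classify MCI. MCI has education-specific MoCA bands (13–14, 19–20, 24–25) and MMSE 24–30. Mild AD has MMSE 21–26. The stage mix is left open.
- **Outcomes.** MoCA and MMSE are two of the five primary scales.
- **Delivery.** "Participants with different degrees of CIs will be assigned to different groups corresponding to their ability". This concerns the running of sessions, not allocation.
- **Analysis.** The section on data collection and analysis plans repeated-measures ANOVA, with adjustment for confounders only where needed. The examples given are age, gender and education.
- **Claim.** The Discussion says "our trial is the first study to assess the effects of an art-based cognitive intervention in different stages of AD".

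**The concern.** Stage is known before anyone is randomised, and it is built partly from scales on which the trial will be judged. If stage is left to chance at allocation and is absent from the model, some of the difference between arms in MoCA or MMSE can simply reflect who had which diagnosis. Between-stage variation also stays in the error term, although the standard deviation used for planning comes from MCI patients alone. A rule that adjusts when needed does not settle the matter. It leaves the covariates to be chosen after the data are seen, and stage and baseline score are not among the examples. What is at stake is precision and a settled primary analysis. Systematic bias is not the issue.

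**Working it through.** **1. The plan's own figure.** Inputs from the sample size section: means 24.68 and 23.13, SDs 1.84 and 1.68, α = 0.05, power 95%. The analysis section makes tests two-tailed.
- Target difference: 24.68 − 23.13 = 1.55.
- Pooled SD: √((1.84² + 1.68²)/2) = 1.762, so d = 1.55/1.762 = 0.88.
- A two-sided two-sample t-test with 35 per arm has power 0.952.
- 35/0.80 = 43.75, rounded up to 44 per arm, 88 in total.

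The stated sample size reproduces.

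**2. How uneven can the arms be?** Assume that K of 88 have mild AD and that each arm has 44. The number in one arm is hypergeometric (88, K, 44).

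| K (assumed) | P(AD share differs by ≥10 percentage points) | P(≥15 points) |
|---|---|---|
| 22 | 22% | 8% |
| 29 | 36% | 17% |

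**3. What is that worth in MoCA points?** The article gives no mean MoCA by stage. Assume equal thirds and a spacing of g points between adjacent stages. The between-stage variance is then (2/3)g², and the chance difference between arms in stage-expected MoCA has SD √((2/3)g² × 2/44). Half the target is 1.55/2 = 0.775.

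| g (assumed) | SD of imbalance | 95% range | P(≥0.775) | P(≥1.55) |
|---|---|---|---|---|
| 2 | 0.35 | ±0.68 | 3% | about 0% |
| 3 | 0.52 | ±1.02 | 14% | 0.3% |
| 4 | 0.70 | ±1.36 | 27% | 2.6% |
| 5 | 0.87 | ±1.71 | 37% | 7.5% |

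Random re-allocation of 88 people in a 29/30/29 mix gives 2.7%, 15% and 25% for P(≥0.775) at g = 2, 3 and 4, close to the normal approximation.

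**4. What does the spread do to precision?** In an unadjusted comparison after treatment, total SD = √(1.762² + (2/3)g²), taking 1.762 as the within-stage SD.
- g = 2: √(3.104 + 2.667) = 2.40. Power at 35 per arm is 76%.
- g = 3: √(3.104 + 6) = 3.02. Power is 56%, and about 100 per arm would be needed for 95%.

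If the model removes the stage component and the within-stage SD is about 1.76, 35 per arm again gives about 95%.

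**5. The planned contrast.** A stage difference that stays constant over time is present at baseline too, so it cancels from a group-by-time contrast. Only stage-related differences in change would remain, and the article gives nothing from which to size them. It also does not say which contrast of the repeated-measures ANOVA is the primary one. Steps 3 and 4 are therefore upper-end figures, for a raw comparison of the kind the sample size assumes.

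**The case against.** Several parts of the opposing case stand.

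- **Silence is not a statement.** The article never says that allocation is unstratified. It condenses a fuller protocol, where lists and strata may be set out. The words about a completely random design describe the sample size formula and do not prove how the list is built. This stands, so any change to allocation has to be conditional. It does not rescue the adjustment rule, which the article does state and states loosely.
- **Chance imbalance is not bias.** Under valid randomisation it belongs to the standard error. This stands: the cost is lost precision.
- **Repeated measures remove much of it.** This stands for the group-by-time contrast, as shown in the working.
- **Education may matter as much.** The article's own MCI bands differ by up to 11 MoCA points across education levels (13–14 against 24–25), and the MMSE ranges for MCI and mild AD overlap. A reader might infer that stage is the strongest predictor of the outcome. The document does not show that, and education belongs in the model as well.
- **Two scales out of five.** The argument is direct for MoCA and MMSE. It is not shown for the depression, anxiety and quality-of-life scales.

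A reader might also infer that a session group could fall below the suggested minimum of 4. With 22 of 88 having mild AD, the chance of fewer than 4 in the intervention arm is 0.007%. It reaches 16% only if about 10 of 88 do. Session groups are in any case formed by ability, not by diagnosis.

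Finally, the reference to different stages in the Discussion describes the population. It does not promise stage-specific estimates.

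**Conclusion.** The point holds as a weakness in how the analysis is fixed, with allocation second. Stage is defined partly by two primary outcome scales, no described step balances it, and neither stage nor baseline score is named for adjustment.

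The size depends on assumptions that the article cannot settle: equal thirds, 2 to 5 MoCA points between adjacent stages, 44 per arm and a raw comparison after treatment. Under these, an imbalance worth half the target effect has a probability of about 3% to 37%. In a group-by-time contrast the effect is smaller.

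A reader might go further and infer that imbalance could rival the target effect itself. That is not supported. At a spacing of 2 to 3 points its probability is below 1%, and it reaches 7.5% only at 5 points. In a two-group version with an assumed 6-point gap between AD and the rest, the arms would have to differ by 1.55/6 = 26 percentage points in AD share. That has a probability of 0.6% with either 22 or 29 AD participants.

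**What to change.** 1. **Primary model.** Replace conditional adjustment with one fixed model for all participants. Include diagnostic stage, the baseline score of the outcome being analysed, and education as covariates, and state which contrast is primary. If baseline enters as a covariate, it should not also be one of the outcome time points. Report the stage-by-treatment estimate as exploratory only, and make no stage-specific claims from it. All these variables are already collected before randomisation, so the cost is a few sentences written before unblinding.
2. **Allocation.** If the full protocol already stratifies by stage, say so in one sentence. If not, use separate concealed lists for SCD, MCI and mild AD, with permuted blocks of varying size, for participants still to be randomised. The cost is three lists in place of one and a short amendment. The small downside is that recruitment has begun, so the scheme changes part-way and the change must be documented. This step is secondary: the fixed model helps every participant, including those already allocated.
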